### RQ2 analyses: Intervention differences

Hypotheses regarding intervention differences are tested using planned comparisons, comparing the postscore outcome measures in the SEMLA and the DIL interventions to each other.

### RQ3 analyses: Mediating effects

Hypotheses regarding mediating effects are tested on the basis of the method proposed by Preacher & Hayes [101]. Preacher & Hayes [101] differentiate between the *total effect* of X on Y, which is the effect when not taking into account the mediator M, the *direct effect* of X on Y, the effect when the mediator is taken into account, and the *indirect effect* of X on Y, the effect of X on Y as mediated by M. In order to estimate the indirect effect, Preacher & Hayes [101] propose a method of fitting the following three regression models:

Y_i_ = α + cX_i_ + ε_i_ where *c* estimates the total effect

M_i_ = α + aX_i_ + ε_i_ where *a* estimates the effect of X on the mediator M

Y_i_ = α + c’X_i_ + bX_i_ + ε_i_ where *c’* estimates the direct effect of X on Y and *b* the effect of M on Y when controlling for X

A prerequisite for a mediation effect is that c is significant (that is, that there is an effect of X on Y at all, that a is significant (that is, that there is an effect of X on M), and that b is significant (that is, there is an effect of M on Y over and above that of X).

The indirect effect, that is, the mediation effect, is equal to the product of a and b, *ab*, which in most cases is equivalent to the difference between c and c’. Several ways of calculating the standard error of ab have been proposed (e.g., [102, 103]; and see [104], for a review). However, following Preacher & Hayes [101], the standard error and significance of ab is calculated on the basis of bootstrapping. Here, ab is calculated on the basis of 10,000 bootstrap samples, yielding a distribution of 10,000 ab estimates. The point estimate of ab is simply the mean of that bootstrapped distribution, the standard error is the standard deviation of the distribution, and the confidence interval is the 5 and 95% percentile of the distribution. The bootstrapped *p* value of ab is the proportion of ab estimates that is equal to or lower than zero and the total number of ab estimates.

In order for a null hypothesis of no mediation effect to be rejected, the effects of a, b, c and ab, as estimated on the basis of bootstrapping, need to be significant.

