	Communication	SEMLA & DIL	EF mediated effect	EF	Communication indice difference	Test of mediation effect
	Language	SEMLA & DIL	EF mediated effect	EF	Language indice difference	Test of mediation effect
	Maths	SEMLA & DIL	EF mediated effect	EF	Maths difference	Test of mediation effect
	EF	SEMLA & DIL	Language mediated effect	Language	Selective attention difference, EF indice difference	Test of mediation effect
	EF	SEMLA & DIL	Maths mediated effect	Maths	Selective attention difference, EF indice difference	Test of mediation effect
RQ4: Moderating effects	EF	SEMLA & DIL	Negative SES moderation	SES	Selective attention difference, EF indice difference	Mixed effects interaction model
	Language	SEMLA & DIL	Negative SES moderation	SES	Language indice difference	Mixed effects interaction model
	Socioemotional skills	SEMLA & DIL	Negative SES moderation	SES	TEC difference	Mixed effects interaction model
	EF	SEMLA & DIL	Negative EF moderation	EF	EF indice	Mixed effects interaction model
	EF	SEMLA	Positive ECERS moderation	ECERS	EF indice	Mixed effects interaction model
	Maths	SEMLA	Positive ECERS moderation	ECERS	Maths difference	Mixed effects interaction model
	Socioemotional skills	SEMLA	Positive ECERS moderation	ECERS	TEC difference	Mixed effects interaction model
	Communication	SEMLA	Positive ECERS moderation	ECERS	Communication indice difference	Mixed effects interaction model
	Language	SEMLA	Positive ECERS moderation	ECERS	Language indice difference	Mixed effects interaction model
RQ5: Background-outcome relationships	Selective attention	SES	Positive relationship	–	Selective attention	Correlational / mixed effects model
	EF	SES	Positive relationship	–	EF	Correlational / mixed effects model
	Language	SES	Positive relationship	–	Language	Correlational / mixed effects model
	Communication	Sex	Higher mean for girls	–	Communication indice	t-test / mixed effects model
	Socioemotional skills	Sex	Higher mean for girls	–	TEC	t-test / mixed effects model
	EF	Sex	Higer mean for girls	–	EF indice	t-test / mixed effects model
	EF	Multilingual	Higer mean for multilinguals	–	EF indice	t-test / mixed effects model
	Maths	Other L1	Higher mean for Swedish L1 children	–	Maths	t-test / mixed effects model
	Socioemotional skills	Language	Positive relationship	–	TEC	Correlational / mixed effects model
RQ6: Background relationships	Preschool time	Preschool start	Negative relationship	–	Preschool time	Correlation / mixed model

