### Power calculations

Power was calculated for each regression coefficient in all of the models described above, in the section about statistical analysis. This was done by refitting each model on 2000 bootstrap /simulation samples, generated as described above. Power statistics were then calculated on the basis of the resulting model coefficient distributions. We calculated mean beta values and also beta confidence intervals, consisting of the 5 and 95% quantiles of each beta coefficient distribution. A beta confidence interval that spans 0 indicates that the effect at hand is non-significant. We also calculated mean *p*-values for the respective coefficients over the 2000 model fits, p-value confidence intervals, consisting of the 5 and 95% quantiles of the distribution of these p-values, as well as bootstrapped p-values, calculated on the basis of the bootstrap distributions of model coefficients. More specifically, bootstrapped p-values are the proportions between the bootstrapped coefficients that span zero and the total number of coefficients (i.e., 2000). For a coefficient C with a mean beta value > 0, boot p-values are the proportion n(C = < 0) by N(C), and for a coefficient with a mean beta value < 0, boot *p*-values are the proportion n(C = > 0) by N(C). Further, the model coefficients that are critical for the hypothesis testing (e.g., the intervention effect coefficients) were adjusted for multiple comparisons, in terms of adjusting for the false discovery rate (see above).

Finally, power was calculated as the proportion of significant p-values (assuming alpha = 0.05) to the total number of 2000 p-values. In other words, power is the percentage of times that the bootstrapped models found the coefficient at hand to be significant.

In the following, we present power analysis statistics for all models testing hypotheses corresponding to research questions RQ1 to RQ5.

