### RQ3 analyses: Mediating effects

As described in more detail above, hypotheses regarding mediating effects are tested on the basis of the method proposed by Preacher & Hayes [101]. Below, we report power analysis statistics for the significance tests of the indirect effect ab from the mediation analyses. These statistics consist of bootstrapping statistics for the beta coefficients (means and confidence intervals), *p*-values (bootstrapped p-values, mean p-values and their confidence intervals), and power calculations. We also present adjusted p-value statistics as well as power calculations as based upon adjusted p-values. It should be stressed, that power calculations were done somewhat differentially than it was done for the coefficients in the mixed effects regression models. In these analyses, the indirect effect ab of a moderation analysis in a given bootstrap sample was deemed significant, firstly, if c, b and a were significant, and secondly, if ab - as estimated by the Sobel test - was significant. Power analyses were therefore conducted on the basis of the p-values of all of these parameters. Adjusted power is calculated on the basis of adjusted p-values of the Sobel test only, although it might be more accurate to also adjust the *p*-values of c, b and a in the power calculation.

Statistics of tests of the indirect effects are shown in Table 5. Apart for the EF mediation effects on the DIL and SEMLA interventions on TEC, these power analyses indicate strong power for all mediation effects under the assumed effect sizes shown Table 3. However, for the math mediation effect on the SEMLA intervention effect on EF (i.e., “EF-by-Math”), the Beta coefficient is negative. This is in line with the previous observation of negative Beta coefficient for the intervention effect of SEMLA on Math. This suggests that the SEMLA intervention effect has a negative impact on children’s early maths skills, which in turn leads to a negative math mediation effect of the SEMLA intervention on EF.

**Table 5 Tab5:** Simulation statistics of the analyses of the indirect effects in the mediation tests, testing mediation effects of EF on the intervention effects on TEC (TEC-by-EF), Language (Language-by-EF), Math (Math-by-EF), the mediation effect of Language on the intervention effect on EF (EF-by-Language), and the mediation effect of Math on the intervention effect of EF (EF-by-Math)

Statistics	TEC-by-EF		Language-by-EF		Math-by-EF		EF-by-Language		EF-by-Math	

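### The RQ3 bootstrap p-value counts only draws at or below zero whatever the sign of ab, so a negative indirect effect gets p near 1; for positive ab it is one-sided, beside a 90% interval

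*Protocol article*

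**What the plan says.** All references are to the protocol article.

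- **RQ3 analyses: Mediating effects (Statistical analysis).** "ab is calculated on the basis of 10,000 bootstrap samples". The p-value "is the proportion of ab estimates that is equal to or lower than zero and the total number of ab estimates", and "the confidence interval is the 5 and 95% percentile of the distribution". The decision rule is a conjunction: "In order for a null hypothesis of no mediation effect to be rejected, the effects of a, b, c and ab" must all be significant. The section does not say whether the p-value or the interval decides for ab.
- **Table 1 (Hypotheses).** The RQ3 rows carry no direction, only entries such as "EF mediated effect". RQ1, RQ2 and RQ4 entries mostly do state one.
- **Adjusting P-values for multiple comparisons.** The Benjamini-Hochberg correction acts on the p-values of the RQ1 to RQ4 tests.
- **Power calculations.** The only alpha appears here ("assuming alpha = 0.05"). The simulation's bootstrap p-value takes the lower or the upper tail according to the sign of the mean coefficient. The simulation intervals are described as "consisting of the 5 and 95% quantiles of each beta coefficient distribution", and the same quantiles are stated for the p-values.
- **RQ3 analyses: Mediating effects (Power analyses).** For the path from SEMLA through Math to EF, "the Beta coefficient is negative", and the text interprets this as a real adverse pathway. Table 5 prints mean −0.59, limits −0.90 and −0.31, boot.p .000 and power 0.82.

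**The concern.** A test of no mediation effect should be able to reject in either direction unless a direction was fixed in advance. The RQ3 rule looks at one tail only, and for a negative ab it is the wrong one: the stronger the negative effect, the closer p comes to 1. A negative path is not hypothetical here, since the article's own simulation produces one and discusses it.

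For a positive ab, the same rule is a one-sided 5% test, and the interval printed beside it covers 90%. The article never says that RQ3 is one-sided. For a negative ab, interval and p-value can point to opposite conclusions, with no statement of which prevails. The article says it sets procedures out before analysis to guard against result fishing, so two conflicting criteria for one test should not remain.

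**Working it through.** **1. The article's own negative path.** Inputs from Table 5, SEMLA, EF-by-Math: mean −0.59, lower −0.90, upper −0.31, boot.p .000. Normal approximation: SD = (upper − lower)/(2z), then P(ab ≤ 0) = Φ(−mean/SD).

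| Reading of limits | SD | P(ab ≤ 0), RQ3 rule | P(ab ≥ 0), tail chosen by sign |
|---|---|---|---|
| 90% (z = 1.645) | 0.59/3.290 = 0.1793 | Φ(3.29) = 0.9995 | 0.0005 |
| 95% (z = 1.960) | 0.59/3.920 = 0.1505 | Φ(3.92) = 1.0000 | 0.0000 |

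The printed .000 is reproduced by the sign-dependent rule of Power calculations. The RQ3 analysis rule applied to the same distribution gives 0.9995 to 1.0000. The limits exclude zero on either reading.

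**2. Positive ab.** p < 0.05 under the RQ3 rule needs z > 1.645 instead of 1.960, which corresponds to a nominal two-sided 2 × 0.05 = 0.10. The 5th to 95th percentile interval covers 95% − 5% = 90%.

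**3. Simulation of the ab test alone.** Assumptions: single level, 216 children in two arms, unit-variance errors, no direct effect, 1,000 trials × 1,000 draws.

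| Setting | RQ3 p-value < .05 | 5/95 interval excludes 0 | Two-sided p < .05 |
|---|---|---|---|
| Null: a = 0, b = 0.6 | 5.4% | 10.5% | 5.8% |
| Negative: a = −0.5, b = 0.5 | 0% | 98.2% | 95.5% |
| Positive: a = 0.3, b = 0.3 | 70.7% | 71.1% | 59.7% |

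The negative row shows the p-value and interval in outright conflict.

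**4. Simulation of the full conjunction.** Assumptions: single level, 280 children in two arms, a, b and c each tested two-sided at .05, 1,500 trials × 600 draws. With a = 0, b = 0.6 and direct effect 0.4, the full rule rejects 2.2% with the RQ3 p-value and 2.7% with a two-sided one. With a, b and the direct effect all 0.3, it rejects 62.5% and 61.1%.

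**5. The quantile label in Power calculations.**

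- *Table 4, EF, SEMLA:* Beta.lower is −0.03 and boot.p is .036. If −0.03 were the 5% quantile, at least 5% of draws would lie below zero and boot.p would be at least .05. A 2.5% quantile is compatible with .036.
- *Table 4, Language, DIL:* power is 0.96, so about 4% of p-values are not significant (at most 4.5% after rounding). The 95% quantile of p must then lie below .05, but p.upper is .080. A 97.5% quantile can be .080.
- *Normal check, Table 4, EF, SEMLA:* SD = 0.67/3.290 = 0.2037 gives tail .070; SD = 0.67/3.920 = 0.1709 gives .040; printed .036.
- *Normal check, Table 6, TEC, SEMLA × SES (0.24; −0.09 to 0.59):* SD = 0.68/3.290 = 0.2067 gives .123; SD = 0.68/3.920 = 0.1735 gives .083; printed .083.

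The first two items are logical bounds that rule out 5/95; the normal checks agree with 2.5/97.5.

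**The case against.** The best defence is that the RQ3 section describes the positive case as shorthand. Power calculations shows that the authors know to switch tails for a negative coefficient, and RQ1 hypothesises positive intervention effects throughout, so a one-tailed mediation test could be defended. The 5 and 95% wording may also be a slip, since the printed simulation intervals evidently are not 5/95. This makes the intention plausible. However, the sign-dependent rule is stated for the simulation only, is itself single-tailed, and does not amend the RQ3 section. Table 1 gives RQ3 no direction.

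Several stronger readings that a reader might infer are not supported:

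- *The RQ3 error rate is 10%.* Rejection also requires a, b and c to be significant. Step 4 gives 2.2% for the full rule, and the choice of p-value hardly changes the positive case.
- *Power for negative mediation is zero.* This holds only if the p-value decides; the interval alone could exclude zero.
- *The rule is what hides suppression.* Where opposing paths cancel, the requirement that c be significant already blocks a finding.
- *Table 5 is wrong.* Its boot.p is taken over 2,000 simulated datasets under its own stated rule, and its power uses the Sobel test. It shows that the two rules differ, not that a planned result was misreported.
- *One-sided and two-sided p-values enter one Benjamini-Hochberg family.* The article states neither a single family for RQ1 to RQ4 nor that the other tests are two-sided.

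**Conclusion.** The concern holds as a defect in a stated rule. As written, a negative ab receives a p-value near 1 (0.9995 to 1.0000 for the article's own example) and cannot be significant on the p-value that the multiplicity correction adjusts, even though its percentile interval excludes zero. For positive ab the p-value is one-sided and the interval is 90%, against a stated alpha of 0.05 and a null without direction. The Power calculations label is also wrong: Table 4 limits cannot be 5/95 quantiles.

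The practical effect on false positives is small because of the conjunction with a, b and c. That judgement rests on the single-level simulation in step 4 and on a, b and c being tested two-sided, which the article does not say. The 0.9995 to 1.0000 rests on a normal approximation to the printed limits; that p would be near 1 follows from the rule itself. RQ1 estimates, including any adverse effect, are untouched.

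**What to change.** In the RQ3 analysis section, replace two sentences: take the 2.5 and 97.5 percentiles as the interval, and define p = 2 × min[P(ab ≤ 0), P(ab ≥ 0)], capped at 1. Then p < 0.05 means that the smaller tail is below 2.5%, which is the condition for the interval to exclude zero, so the two criteria agree in both directions.

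The cost is that p-values for positive ab double. An ab with between 2.5% and 5% of draws at or below zero would no longer pass; under the full conjunction in step 4 that moved rejection from 62.5% to 61.1%.

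In Power calculations, correct the 5 and 95% quantile label to 2.5 and 97.5 after checking the simulation code. No power figure changes, because power was computed from model p-values or the Sobel test. The boot.p values in Tables 4 to 7 need not be doubled, since that section already defines them as single-tail; a note calling them one-sided would be enough.

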### RQ1 analyses: Intervention effects

For RQ1 hypotheses, mixed effects modelling will be used to test the null hypotheses that there are no intervention effects on each of the respective outcome variables. Mixed effects modelling allows for the inclusion of multiple hierarchically nested random effects, such as children nested within preschool units and preschool units nested within preschools (e.g., [100]). The mixed effects model can thereby account for systematic influences of preschool units or preschools on the outcome variables. The model formula for the RQ1 hypothesis analyses is:

$$ {\mathrm{POSTSCORE}}_{\mathrm{ijk}}=\kern0.5em {\upalpha}_{0\mathrm{jk}}+{\upalpha}_{00\mathrm{k}}+{\upbeta}_1{\mathrm{INTERVENTION}}_{0\mathrm{jk}}+{\upbeta}_2{\mathrm{Y}}_{\mathrm{ijk}}+{\upbeta}_3{\mathrm{PRESCORE}}_{\mathrm{ijk}}+{\upbeta}_4{\mathrm{FIDELITY}}_{\mathrm{ijk}}+{\upbeta}_5{\mathrm{ECERS}}_{00\mathrm{k}}+{\upvarepsilon}_{\mathrm{ijk},}\ {\upvarepsilon}_{\mathrm{ijk}}\sim \mathrm{N}\left(0,{\upsigma^2}_{\upvarepsilon \mathrm{ijk}}\right),{\upalpha}_{\mathrm{j}}\sim \mathrm{N}\left(0,{\upsigma^2}_{\upalpha \mathrm{j}}\right),{\upalpha}_{\mathrm{k}}\sim \mathrm{N}\left(0,{\upsigma^2}_{\upalpha \mathrm{k}}\right) $$

In the models, the *i*th child is nested within the *j*th preschool unit, which in turn is nested within the *k*th preschool.

These models predict the postscore of the given outcome measure for child *i* as a function of the intervention administered at preschool unit *j*, using the control intervention as the baseline category. They also control for the set of background variables Y of child *i*, as well as the prescore measure of child *i*, centered around zero, as well as the fidelity score for child *i*, as explained in more detail above. Further, they control for the total ECERS rating of preschool *k*, thereby taking into account any influence of preschool quality on the outcome variables. Finally, they include individual intercepts α for each preschool *k*, as well as individual intercepts α for each preschool unit *j*, thereby controlling for systematic differences between preschool units and preschools with respect to the outcome variables.

Separate models will be conducted on selective attention, early maths skills and emotional comprehension, as well as on the composite measures of EF, language and communication.

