**Fig. 1 Fig1:**
[figure not shown]
The relationship between EFScore and Age in the pilot data set and a bootstrapped data set with noise adjustment set to 0.5 standard deviations. Colours differentiate between children in the original pilot data. Diamonds illustrate data points in the pilot data set and dots show bootstrapped data points. The dashed regression line illustrates the linear fit in the bootstrapped data set, and the dotted line the pilot data set

In addition to adding noise to the data, the dependent measures were adjusted for intervention main effects. This was done by adjusting the difference between the pre-, x_pre_, and post, x_post_ measurements of the aforementioned dependent measures so that they differed in strength in accordance with some adjustable effect size δ. More specifically, the mean difference between pre- and post-measurements was added to each post-measurement data point, i.e., x_post_ = x_post_ + Σx_pre_ / n_pre_ - Σx_post_ / n_post_, in order to ensure no initial difference between mean pre- and post-measurements. Then, the pooled standard deviation over interventions, σ, was calculated. Individual post-measurements were then increased in accordance with its effect size on the basis of the pooled standard deviation, i.e., x_post_ = x_post_ + δσ. Table 3 shows the effect size adjustments used for each intervention and each of the adjusted dependent measures. The table illustrates small, most likely insignificant, effects in the control intervention, strong EF effects but weak language and emotional comprehension effects in the DIL intervention, and, on the other hand, weak EF effects but strong emotional comprehension and language effects in the SEMLA intervention.

**Table 3 Tab3:** Effect size adjustment δ for each intervention and dependent measure

Dependent Variable	Control	DIL	SEMLA
DCCSScore	0.1	0.5	0.3
FlankerScore	0.1	0.5	0.3
HeadShoulders	0.1	0.5	0.3
Math	0.1	0.5	0.3
FDS	0.1	0.5	0.3
TEC	0.1	0.2	0.6
PPVT	0.1	0.3	0.5
LangPredicates	0.1	0.3	0.5
LangSubordinates	0.1	0.3	0.5
LangEvents	0.1	0.3	0.5

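### RQ3 mediation models are printed without cluster terms, and Table 5 reports as power a rejection rate from data with no mediator-to-outcome path built in

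*Protocol article*

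**What the plan says.** Under the RQ3 heading of the statistical analysis section, the article adopts "a method of fitting the following three regression models". The first two read "Y_i_ = α + cX_i_ + ε_i_ where *c* estimates the total effect" and "M_i_ = α + aX_i_ + ε_i_ where *a* estimates the effect of X on the mediator M". All three have a child index only, with no unit intercept, preschool intercept, prescore or background variable. The decision rule is "In order for a null hypothesis of no mediation effect to be rejected, the effects of a, b, c and ab" must all be significant.

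The RQ1 and RQ4 models, by contrast, carry random intercepts for unit and preschool and a prescore. Table 1 names pre-post difference measures for the RQ3 outcomes. It lists EF as mediator for language and maths, and language and maths as mediators for EF.

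Under Data simulation, effects are created measure by measure: "Individual post-measurements were then increased in accordance with its effect size on the basis of the pooled standard deviation". The RQ3 power section says that "power calculations were done somewhat differentially than it was done for the coefficients in the mixed effects regression models". It sets aside the two TEC-by-EF effects and concludes that "these power analyses indicate strong power for all mediation effects under the assumed effect sizes shown Table 3".

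**The concern.** There are two separate problems.

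- **Clustering.** X varies only between units, so a regression that treats children as independent understates the standard errors of a and c. The same intervention effect would then be tested under RQ1 with clustering and under RQ3 without it.
- **What the rule detects.** Mediator and outcome are measured over the same pre-post interval. If an intervention improves two outcomes in parallel, and those outcomes correlate between children, then a, b, c and ab can all be significant with nothing passing from one outcome to the other. The same data can satisfy the rule in both directions.

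At stake is the RQ3 conclusion: parallel improvement could be reported as mediation, supported by a power table that appears to validate the method.

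**Working it through.** **1. Table 5 against the way its data were built.** The simulated sample is 9 clusters × 3 arms × 12 children = 324, as stated. Table 3 gives each measure its own shift by arm (Control/DIL/SEMLA: EF components and maths 0.1/0.5/0.3, language components 0.1/0.3/0.5). No term carries a shift in one outcome on to another. The DIL powers in Table 5 are:

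| Pair | EF as mediator | EF as outcome |
|---|---|---|
| EF and language | 0.97 | 0.97 |
| EF and maths | 0.99 | 0.99 |

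Opposite directions are declared almost equally often. Table 5 cannot be recomputed exactly, because the pilot data and covariances are not given.

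**2. Type I error of a and c as printed.** Mean unit size is 432/28 = 15.4. With design effect DE = 1 + 14.4 × ICC, the naive two-sided rejection rate is 2(1 − Φ(1.96/√DE)). The article gives no ICC, so a range is assumed:

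| ICC | DE | Rejection rate |
|---|---|---|
| 0.02 | 1.29 | 8.4% |
| 0.05 | 1.72 | 13.5% |
| 0.10 | 2.44 | 21% |

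**3. The rule with no mediator-to-outcome path.** A Monte Carlo check compared one active arm with control, using 9 clusters of 12 per arm, separate shifts in M and Y, ordinary least squares, and a requirement that a, b, c and the Sobel test all be significant. Assumptions: M-Y correlation 0.2 to 0.6, ICC 0 or 0.10, pre-post stability 0.7. The Table 3 shifts relative to control (0.4 and 0.2 per component), summed over four components with an assumed inter-item correlation of 0.3, become 1.6/√7.6 = 0.58 for EF and 0.8/√7.6 = 0.29 for language.

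| Shifts | Post scores | Difference scores |
|---|---|---|
| Table 3 (0.58, 0.29), EF as mediator | 34–57% | 47–80% |
| Table 4 betas (0.85, 0.49), EF as mediator | 62–95% | 72–99.8% |
| Table 4 betas, direction reversed | 49–95% | 62–99.8% |

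**4. Table 5 against Table 4.** A rule requiring several tests to be significant cannot have more power than the weakest of them. In Table 4, DIL on TEC has power 0.17 and SEMLA on EF 0.69. In Table 5, TEC-by-EF under DIL has 0.51. The five SEMLA entries run from 0.75 to 0.82, and each needs SEMLA on EF, as a in three and as c in two. The a and c of RQ3 were therefore not taken from the RQ1 models.

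**5. What the cluster and pretest terms repair.** With shifts of 0.85 and 0.49 and ICC 0.10, cluster-robust errors plus both pretests reduced the false-mediation rate from 36–86% to 6–18% when M and Y are linked only by a stable trait. When they also share occasion-specific variance, the rate was 61–88% as printed and 61–93% afterwards. With no effect on M, the rejection rate for a fell from 0.10, 0.18 and 0.29 (ICC 0.05, 0.10, 0.20) to 0.06.

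**The case against.** The equations are introduced as the general form of a cited method, and no sentence says that random intercepts are left out. The Discussion describes mixed modelling as the way the hierarchy is handled. This stands as a caution: the single-level reading is what is printed, and the power section's separation of mediation from the mixed models supports it, but it is not certain.

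Several stronger readings are tempting and are not supported:

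- **That RQ3 ignores the pretest.** Table 1 names difference scores, so the pretest may enter through the measure. The fault is that Table 1 and the equations differ. Step 3 shows that difference scores do not remove the false mediation.
- **That Tables 4 and 5 contradict each other.** The RQ1 models adjust for prescore, background variables, fidelity and ECERS. If RQ3 does not, different power is expected. The comparison shows only that RQ3 does not use the RQ1 estimates.
- **That b cannot be estimated.** The third equation prints b on X, but the same line defines b as the effect of M. It is a misprint.
- **That the simulated data are a clean no-mediation null.** Data are resampled by pilot arm, and pilot differences carry over: the SEMLA beta on maths is −0.08 although Table 3 assigns 0.3 against 0.1 for control. What can be said is that no mediator-to-outcome path was specified.
- **That false mediation is nearly certain.** The highest rates use Table 4 betas; the Table 3 shifts give 34–80%. Table 5 and step 3 use the Sobel test where the plan uses a bootstrap, and steps 2 and 3 do not apply the Benjamini-Hochberg correction planned for RQ1 to RQ4.

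**Conclusion.** The point holds and should be fixed. As printed, RQ3 omits the clustering that the allocation requires, and its a and c tests are then anti-conservative to the extent shown in step 2, given the assumed ICCs. Independently of clustering, the decision rule can be met by parallel effects on correlated outcomes, and Table 5 does not show power to detect a specified mediation effect. The false-mediation rate cannot be fixed from the article: roughly one third to nearly all simulated trials, depending on effect sizes, M-Y correlation and ICC.

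Confidence is high on the Table 5 interpretation and moderate on clustering, which rests on the equations being applied as printed. RQ3 is one of seven questions in a design described as partly exploratory.

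**What to change.** - Fit the a, b and c models with the RQ1 unit and preschool intercepts and baseline covariates, plus the prescores of both M and Y. Correct the third equation so that b multiplies M, and reconcile the equations with the difference scores in Table 1.
- Bootstrap clusters rather than children: resample units within arm, or whole preschools stratified by their allocation pattern. Resampling preschools simply within arm is undefined, because one preschool may hold both an intervention and a control unit.
- Present RQ3 as exploratory indirect association, report both directions of each pair together, and state that contemporaneous M and Y cannot establish direction. The model changes correct a and c but do not make b causal.
- Stop describing Table 5 as power for mediation. Relabel it as the rejection rate with no mediator-to-outcome path built in, or replace it with the rejection rate under no mediation and the power under a stated path.

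The cost is analysis code and wording, with wider intervals and a weaker RQ3 claim. No new data are needed.
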